#### Staff and volunteers

In consultation with operational and clinical management at each site, a hospice study lead has been identified through whom the following denominators will be established:

Number of staff working on or rotating through the in-patient unit of the hospice.Number of volunteers active within the in-patient unit of the hospice.Total number of documented in-patient delirium episodes or (if total number cannot be established) number of patients with at least one case-note diagnosis of delirium per in-patient admission in the hospice.

Level of staff engagement with CLECC-Pal during the implementation period will be assessed weekly by the hospice study lead completing a rapid report of numbers of:

Staff indirectly involved in delivering delirium care who attend the team study day, action learning sets, feedback following peer observations of practice, mid-shift cluster discussions, and reflective discussions.Staff and volunteers who do not engage with CLECC-Pal.Staff and volunteers who decrease or stop their engagement with CLECC-Pal.Peer observations of practice achieved.People approached, reported by professional group and role, who agree to participate in using CLECC-Pal.

The rapid report will also record reasons for:

Staff and volunteers’ non-engagement or dropout.Modifications made in the use of CLECC-Pal.

Quantitative data will be analysed descriptively using radar plots. Qualitative data will be rapidly analysed deductively using a Framework approach.^30^ Analyses will inform more detailed exploration in interviews (WP3) and will be shared with participating hospices to inform their ongoing use of CLECC-Pal.

#### Economic

We will assess the feasibility of collecting data about the costs of using CLECC-Pal:

Number of hours spent by members of staff and volunteers in CLECC-Pal activities, linked to pay-grade where possible.

### WP 3: realist process evaluation

Critiques of process evaluations have highlighted the importance of methods that can use theory to explore how contexts and mechanisms interact,^31–33^ as recognised in the revised Medical Research Council framework.^34^ We shall use realist evaluation^35^ to capture staff and management insights into how individual-level, team-level and organisational-level contexts affect these interactions during implementation,^36^ refining normalisation process theory’s (NPT) propositions about the mechanisms of coherence, cognitive participation, collective action and reflexive monitoring.^37–39^ Definitions of realist terms are shown in table 5. This theoretically informed understanding of how the implementation strategy functions^40^ will enable us to explain how hospices may operationalise CLECC-Pal in different ways to achieve the same desired outcomes (eg, by running online learning rather than a team study day, or using self-reflection on practice rather than peer observation).

**Table 5 T5:** Definition of realist terms used in work package 3

Term	Definition
Context	Individual, team, organisational or other factors that enable or constrain the operation of mechanisms.^53^ This includes social phenomena such as rules, norms and values, meaning that contexts are not straightforwardly analogous with settings.^54^
Mechanism	The interaction of a programme’s resources or opportunities with individuals’ or teams’ reasoning.^53^
Outcome	The ‘demi-regular’ occurrences arising from particular configurations of contexts and mechanisms.^47^ Consistent with the recognition in realist ontology of the dynamic and non-linear nature of open systems in the social world,^55^ ‘outcomes’ may be better understood as semistable processes.
Programme theory	A middle-range theoretical explanation of how (implementation) programme activities relate to underlying theory. Even if not explicitly stated, programme theories contain ideas about how best to address challenges to achieving intended goals (including how to proactively manage these challenges)^56^

### Identification, sampling and consent

#### Surveys

All hospice staff involved in direct patient care or management, as well as those directly involved in patient care (volunteers, support staff, board members with a hospice governance role) will be eligible. Minimum sample size of 10 at each hospice (total n=30). Eligible participants will be sent a link to the anonymous survey, for which completion online will be taken as implied consent.

#### Interviews

A purposive sampling strategy at each site will draw from a sampling frame that includes all hospice staff involved in direct patient care or management, volunteers, support staff and board members at each study site. Within the constraints of an exploratory sample size (five staff and volunteers, and two members of management and/or executive board at each site; minimum total n=15), we shall endeavour to maximise variation in participant characteristics and roles, prioritising sampling that will enable comparison between those who do and do not take part. Written informed consent will be obtained. Interviews will be conducted at a time suitable for participants and may be face to face or remote, according to participant preference.

### Data collection and analysis

#### Staff and volunteers’ preimplementation and postimplementation experiences (survey)

Survey using a modified and piloted normalisation measurement instrument (NoMad).^41^ of staff and volunteers’ perceptions and experiences of implementation, in relation to each NPT mechanism, before and after using the CLECC-Pal implementation strategy.

Quantitative Likert scale responses will be analysed descriptively using radar plots. Free-text responses will be deductively thematically analysed using the framework of NPT mechanisms (coherence, cognitive participation, collective action and reflexive monitoring), allowing for inductive thematic analysis if responses do not fit within the framework. Thematic patterns and outliers will be identified. The analysis will also inform the structure, content and focus of the staff and volunteer interviews.

#### Staff and volunteers’ postimplementation experiences (interviews)

Realist interviews are distinct from conventional qualitative semistructured interviews as they adopt a ‘teacher-learner’ approach. This involves presenting theory to participants so that they can communicate their own experiences and views that may refute, refine, or expand the theory.^42^ In practice, the realist interviewer presents theory (context-mechanism-outcome configurations) in a form comprehensible to the participant and follows-up flexibly with further questions tailored to the participant’s understanding, to ensure that the discussion enables theory-refinement rather than simply a discussion of experiences. Interviews will build on Murray *et al*’s^43^ operationalisation of NPT for the development and optimisation of interventions within trials (see table 6).

**Table 6 T6:** Normalisation process theory ‘contribution’ mechanisms and their relationship to data collection in interviews

Mechanism	Definition^37^	Theoretical propositions^38^	Potential interview questions^43^
1. Coherence	Agents attribute meaning to a complex intervention and make sense of its possibilities within their field of agency. They frame how participants make sense of, and specify, their involvement in a complex intervention.	1.1 Embedding is dependent on work that defines and organises a practice as a cognitive and behavioural ensemble. 1.2 Embedding work is shaped by factors that promote or inhibit actors’ apprehension of a practice as meaningful. 1.3 The production and reproduction of coherence in a practice requires that actors collectively invest meaning in it.	Is CLECC-Pal: easy to describe? clearly distinct from other strategies? have a clear purpose for all participants? Do participants have a shared sense of purpose? What benefits will the intervention bring and to whom? Are these benefits likely to be valued by potential participants? Will CLECC-Pal fit with the overall goals and activity of the organisation?
2.Cognitive Participation	Agents legitimise and enrol themselves and others into a complex intervention. They frame how participants become members of a specific community of practice.	2.1 Embedding is dependent on work that defines and organises the actors implicated in a practice. 2.2 Embedding work is shaped by factors that promote or inhibit actors’ participation. 2.3 The production and reproduction of a practice requires that actors collectively invest commitment in it.	Are target user groups likely to think that CLECC-Pal is a good idea? Will they see the point of CLECC-Pal?
3. Collective Action	Agents mobilise skills and resources and enact a complex intervention. They frame how participants realise and perform the intervention in practice.	3.1 Embedding is dependent on work that defines and operationalises a practice. 3.2 Embedding work is shaped by factors that promote or inhibit actors’ enacting it. 3.3 The production and reproduction of a practice requires that actors collectively invest effort in it.	How will CLECC-Pal affect the work of user groups? Will CLECC-Pal promote or impede their work? Will staff require extensive training before they can use CLECC-Pal? How compatible with existing work practices is CLECC-Pal? What impact will CLECC-Pal have on division of labour, resources, power, and responsibility between different professional groups? Will CLECC-Pal fit with the overall goals and activity of the organisation?
4. Reflexive Monitoring	Agents assemble and appraise information about the effects of a complex intervention within their field of agency, and use that knowledge to reconfigure social relations and action. They frame how participants collect and use information about the effects of the intervention.	4.1 Embedding is dependent on work that defines and organises the everyday understanding of a practice. 4.2 Embedding work is shaped by factors that promote or inhibit appraisal. 4.2 The production and reproduction of a practice requires that actors collectively invest in its understanding.	How are users likely to perceive CLECC-Pal once it has been used for a while? Is CLECC-Pal likely to be perceived as advantageous for patients or staff? Will it be clear what effects CLECC-Pal has had? Can users contribute feedback about CLECC-Pal once it is in use? Can CLECC-Pal be adapted or improved on the basis of experience?

CLECC, Creating Learning Environments for Compassionate Care.

Interview topics will include, but not be limited to, experiences of CLECC-Pal’s acceptability and fit, rationale for any modifications to CLECC-Pal, perceived changes in communication between those caring for patients at-risk of delirium, changes in care practices, perceptions about how CLECC-Pal is achieving (or not) the intended effects and, if appropriate, how these impacts could be sustained. Interview questions will be informed by emerging site-specific data from the codesign and feasibility WPs, as well as from the process evaluation survey. Graphical summaries of data, such as radar plots, will be used in the interviews to communicate this emerging data to participants, link to theory and to support discussion that enables implementation theory to be refined.^42 44^ Views of study processes will also be sought. It is envisaged that interviews will last no longer than 30 min, but participants will be given the opportunity for a longer interview if they wish.

Interviews will be recorded and transcribed. Before commencing analysis, interview transcripts will be read and reread to allow familiarisation with the content that will enable theory-building and refinement rather than rote coding of contexts, mechanisms and outcomes (although coding of these configurations may also play an important role in theory-building and refinement). Analysis to identify contextualised explanations of how mechanisms of implementation are understood to lead to certain outcomes will be structured using the reasoning processes identified by Pawson (juxtaposition, reconciliation, adjudication, consolidation and situating^45^). We shall operationalise these reasoning processes using the analytic questions for building and refining programme theory identified by Pearson *et al.*^46^

WP 3 methods and findings will be reported consistent with the RAMESES reporting standards.^47^

## Ethics and dissemination

Ethical approval for the study has been obtained from Hull York Medical School Ethics Committee (Ref.: 21/23), Health Research Authority Research Ethics Committee Wales REC7 (Ref.: 21/WA/0180) and Health Research Authority Confidentiality Advisory Group (Ref.: 21/CAG/0071). Confidentiality advisory group approval allows the study researcher access to the clinical records to extract data without patient consent. The study is publicised in the hospices during the data collection period and patients/representatives may opt out if they do not wish their data to be used. Written informed consent will be obtained from interview participants.

he primary objective of this study is to inform a future quasi-experimental multi-site comparative evaluation. We shall do this by demonstrating the feasibility (or otherwise) of the implementation strategy (‘intervention’), participant recruitment and data collection, in addition informing decisions about the most appropriate study design for a future multisite comparative evaluation. However, as argued by Thabane *et al*^48^ communicating findings from feasibility studies remains critically important for ensuring that resources are not spent on either duplicating the feasibility study or funding research uninformed by the findings of a relevant feasibility study. We shall therefore prepare a full report of the study’s methods and findings for the funder and submit a manuscript reporting the findings to an open access peer-reviewed journal. The study’s findings will also be submitted for oral presentation at one national health services research conference and one international palliative care conference. A Plain English summary of study findings will be prepared for distribution through palliative care clinical networks (including Hospice UK) and public involvement groups.

## Discussion

This study will address key uncertainties about the implementation of guideline-adherent delirium care in hospices—the feasibility of using a theoretically informed, codeveloped implementation strategy (CLECC-Pal); collecting demographic, diagnostic and delirium management data from clinical records; collecting measures of staff engagement; and collecting explanatory process data about staff use of CLECC-Pal. This will enable us to estimate the number of hospice sites and in-patient episodes needed for the planned national quasi-experimental study, for which we outline the design considerations below. The study has clear strengths in public involvement and in minimising research waste by using existing process and outcome data. There are also limitations in the study, for example, hospices are all drawn from a single region of the UK and the sample size for surveys and interviews may limit the extent to which the complexity of staff and management characteristics, views and experiences can be explored. Nevertheless, the study hospices have diverse characteristics (locations, level of socio-economic deprivation, forms of governance) and we shall purposively sample staff and management (for interviews) to maximise the range of professional and role characteristics.

We have developed this feasibility study to inform future decisions about evaluative study design that balances scientific rigour and practical considerations. In doing so, we first appraised an interrupted time series design that would enable naturalistic data collection, but considered this unrealistic as powering the study would likely require 12 months preintervention and postintervention data collection.^49^ Second, we appraised a randomised stepped wedge design, but considered implementation research permutations of this design unlikely to be feasible due to the real-world setting (if using a head-to-head rollout design) or length of time required (if using a pairwise enrolment rollout design).^50^

Consistent with current thinking in implementation research for investigators to consider quasi-experimental study designs that can assess the impact of context over time,^51^ we plan to work towards an evaluative study design that uses natural variation in the introduction of the implementation strategy to allow a non-randomised stepped wedge design (CLECC-Pal supported delirium care vs delirium care as usual). Our audit data indicate that this would be realistic given an annual admission rate of 192–384 in the 10–20 bedded study site hospices which have a 40%–60% incidence of delirium.

While hospices are relatively homogeneous in terms of care delivery by health professionals (eg, standardised national training programme for doctors, national standards for nursing practice), the wide referral base of hospices mean that in-patients tend to be heterogeneous in relation to type and stage of disease, ethnicity, socioeconomic status and so on. For the future evaluative study, we shall estimate the intraclass correlation coefficient using preintervention patient outcome data (delirium-free days) from the feasibility study, thus enabling a sample size calculation powered on the primary outcome for the future evaluative study.

We are mindful of a recent systematic review of feasibility studies which identified a lack of consistency in the use of terminology, a predominance of feasibility issues relating to preparation for randomised-controlled trials, and an absence of clear guidance about when ‘sufficient insight about uncertainties’ had been achieved for progression to an evaluation study.^52^^p.10^ However, we are confident in stating minimum recruitment targets for the use of CLECC-Pal (fidelity to core components) and 4AT screening tool at baseline and daily, that will be necessary for a future evaluative study to be considered feasible:

≥80%, proceed.60%–80% with mitigating factors, proceed.<60% not feasible.

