### Aims and objectives

This study will address key uncertainties about the implementation of guideline-adherent delirium care in hospices by demonstrating if it is possible to:

Coadapt an implementation strategy (CLECC) for use in hospices (work package 1, WP).Systematically and reliably collect data (including delirium diagnosis) from clinical records in a way that minimises burden for patients, families and staff (WP 2).Collect measures of staff engagement with the implementation strategy, delivery of guideline-adherent delirium care, and the costs of staff involvement (WP 2).Collect explanatory process data about staff use of the implementation strategy (WP 3).Estimate the number of hospice sites and in-patient episodes needed for the planned national quasi-experimental study.

WP 1 commenced June 2021, with WP 2 and 3 (and data collection) commencing August 2021. The study will be completed in February 2023.

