### Settings

Three adult hospices in northern England (UK). Two hospices in this study are located in socio-economically deprived urban areas (one with a significant minority ethnic group population) and one hospice in an affluent rural/urban area. One hospice is run by a national charity, with the other two hospices run by independent charities.

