### Data collection and analysis

#### Patients

Baseline and follow-up (pre and post) clinical record data will be collected. Data will be collected through remote access to the clinical record where electronic records allow, or from the paper record. At each of the three hospices, case note collection (total n=300) will comprise:

Baseline (pre): 50 consecutive patients who completed their in-patient stay immediately prior to the start of the hospice using CLECC-Pal.Follow-up (post): 50 consecutive patients completing their in-patient stay from week 4 of starting use of CLECC-Pal.

Clinical record data collected by the researcher will be anonymised at the point of extraction and include:

Demographic data (baseline only): age, sex, main medical condition, ethnicity, postal code (converted to Index of Multiple Deprivation (IMD) score).Delirium diagnosis using the Inouye *et al* case note tool.^23^Delirium management: including evidence of use of delirium screening tools, risk assessments and individualised delirium management care plans.

Clinical record data will be extracted using an expanded version of the prospectively validated (74% sensitivity, 83% specificity) chart-based instrument developed by Inouye *et al* for detecting potential delirium diagnoses from clinical records.^23^ The instrument (data extraction proforma, see online supplemental file 1) will enable us to assess whether case-note recorded symptoms of delirium (and therefore number of patient days with delirium) can be linked to time points during the person’s admission when actions around delirium assessment, management and prevention (consistent with guidelines) did or did not take place. Our ‘expanded’ version of the instrument will include questions about other actions to support delirium assessment, management and prevention that may be recorded in the notes, as shown in table 4. We shall report the percentage of clinical records where information about each of these actions is recorded. Where a person experiences multiple episodes of delirium within one admission, each episode will be recorded separately and linked through the anonymised case number.

10.1136/bmjopen-2021-060450.supp1Supplementary data

**Table 4 T4:** Additional delirium assessment items to be derived from clinical records and means of assessing feasibility of data collection

Delirium-related action	Assessment of feasibility

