Use of richmond agitation-sedation scale and 4AT screening tools	% completed % reassessments completed at appropriate timepoints
Medication reviews (to minimise deliriogenic medication)	% completed % reassessments completed at appropriate timepoints
Diagnostic and Statistical Manual of Mental Disorders (DSM-V) delirium assessment	% completed % reassessments completed at appropriate timepoints
Degree of sedation or agitation	% completed
Individualised delirium care plans	% completed % reviewed at appropriate timepoints
Presence/absence of delirium	% documenting start and end of delirium episode(s) % documenting delirium-free days

Where judgements about what to record on the pro-forma need to be made, justification for these will be recorded on the form. Any uncertainty about how the information in the case notes should be recorded on the proforma will be discussed with a second clinician (CJ) and justification for the final decision recorded.

The number of patient records from which it was possible to extract clinical record data longitudinally over the duration of their inpatient admission will be reported both as a simple count and as a percentage of the total number of in-patients with a diagnosis of delirium in each hospice each month.

Sample size: Based on our pilot work in one hospice (comparable in size to the hospices in this study) which identified a monthly occurrence of 32 inpatient episodes of delirium, retrospectively collecting clinical record data for all patients whose episode of in-patient care is completed (up to a maximum of 50 per hospice) will provide us with enough data to answer feasibility questions about data quality and enable us to capture frequent events regarding care planning. We do not propose to investigate less-frequent events such as antipsychotic use.

Analysis: Baseline demographic and clinical characteristics of the study population (age, sex, primary medical condition, ethnicity, postal code (to derive IMD)) will be presented using descriptive statistics. Mean (SD) will be reported for continuous data and raw count (number, percentage) will be reported for nominal data. The variation around baseline delirium days will be calculated to inform the sample size and number of hospices needed for the subsequent national study.

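### An intraclass correlation from three hospices in one period is too imprecise to support the sample size calculation for the national study that the Discussion says it enables

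*Protocol article*

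**What the plan says.** The fifth item under Aims and objectives is to "Estimate the number of hospice sites and in-patient episodes needed for the planned national quasi-experimental study".

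The Discussion says how the clustering input will be obtained: "we shall estimate the intraclass correlation coefficient using preintervention patient outcome data (delirium-free days) from the feasibility study". It then states the result: "thus enabling a sample size calculation powered on the primary outcome for the future evaluative study". The intended design uses natural variation in when hospices introduce the strategy, "to allow a non-randomised stepped wedge design".

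The data behind this estimate are fixed in two places. Settings names three adult hospices in one English region. The Patients section of work package 2 sets the pre-intervention block at each hospice: "Baseline (pre): 50 consecutive patients who completed their in-patient stay immediately prior to the start of the hospice using CLECC-Pal". The sample size paragraph of the same section treats 50 as a ceiling ("up to a maximum of 50 per hospice").

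The limitations listed at the front of the article and in the Discussion cover the single region and the size of the survey and interview samples. The precision of the ICC is not among them.

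**The concern.** An ICC compares variation between hospices with variation within them. How well the between-hospice part is known depends on the number of hospices, and extra records per hospice hardly help. Three hospices give 2 degrees of freedom, so the estimate could fall almost anywhere in the plausible range. The article nevertheless says that it makes a powered calculation possible.

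There is a second gap. The power of a stepped wedge depends on the correlation of outcomes within a hospice in the same period and also on how far that correlation persists from one period to the next. A single pre-intervention block carries no information on persistence, however many hospices contribute.

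At stake is the fifth aim. If the point estimate is taken at face value, an estimate near zero would lead to a national study with too few hospices. A large chance estimate could make a workable study look unaffordable.

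**Working it through.** **Plan's own figure.** 3 hospices × (50 baseline + 50 follow-up) = 300 records, which matches the stated total. The ICC uses the baseline half, 3 × 50 = 150. The article gives no ICC, target effect, power or national sample size, so the ICC values below are assumptions, shown as a range.

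**Step 1: confidence interval for the ICC.** Use a balanced one-way analysis of variance with a normal outcome, k = 3 hospices and m = 50 records. The degrees of freedom are k − 1 = 2 and k(m − 1) = 147.

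- F that corresponds to an observed ICC r: F = (1 + 49r)/(1 − r). For r = 0.05, F = 3.45/0.95 = 3.63.
- The 97.5% and 2.5% points of F(2,147) are 3.783 and 0.02532. Dividing, F_L = 3.63/3.783 = 0.960 and F_U = 3.63/0.02532 = 143.4.
- Limits: (F_L − 1)/(F_L + 49) = −0.0008, taken as 0, and (F_U − 1)/(F_U + 49) = 0.74.

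| Observed ICC | 95% CI, 3 hospices × 50 |
|---|---|
| 0.01 | 0 to 0.54 |
| 0.02 | 0 to 0.61 |
| 0.05 | 0 to 0.74 |
| 0.10 | 0.014 to 0.84 |

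The number of hospices is what limits precision. At an observed ICC of 0.05 with 50 records each, 10 hospices would give 0.014 to 0.18 and 30 would give 0.025 to 0.10. Since 50 is a ceiling, smaller blocks are possible: with 20 records at each of three hospices the interval is 0 to 0.80.

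**Step 2: chance of an estimate at or below zero.** The estimate is ≤ 0 when the observed F is ≤ 1. If the true ICC is ρ, this probability is Pr[F(2,147) ≤ (1 − ρ)/(1 + 49ρ)].

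| Assumed true ICC | Pr(estimate ≤ 0) |
|---|---|
| 0.01 | 48% |
| 0.02 | 39% |
| 0.05 | 24% |
| 0.10 | 14% |

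At a true ICC of 0.05, simulation (100,000 runs) puts the central 95% of estimates between −0.02 and 0.20 with a median of 0.03, so the typical error is downward.

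**Step 3: the within-hospice SD, for contrast.** With 147 degrees of freedom, the 95% limits for the true SD divided by its estimate are √(147/χ²), which gives 0.90 and 1.13. The SD is therefore known to about −10% to +13%. The weakness is specific to the ICC.

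**Step 4: what a wrong ICC costs in a stepped wedge.** The article gives no layout, so one is assumed: 12 hospices, 5 periods and equal numbers crossing over at each of 4 steps. The generalised least squares variance of the effect, with period terms, is expressed relative to an individually randomised trial of the same size.

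| Patients per hospice-period | Between-period autocorrelation | ICC 0 | ICC 0.05 | ICC 0.20 | Ratio, 0.05 to 0 |
|---|---|---|---|---|---|
| 10 | 1 | 2.00 | 2.68 | 2.54 | 1.3 |
| 10 | 0.8 | 2.00 | 2.85 | 3.68 | 1.4 |
| 50 | 0.8 | 2.00 | 4.46 | 8.94 | 2.2 |

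Planning on ICC 0 when the truth is 0.05 therefore understates the variance about 1.3- to 2.2-fold. The autocorrelation matters as well: at 10 patients per period and ICC 0.20, moving it from 1 to 0.8 raises the relative variance from 2.54 to 3.68.

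**The case against.** The best defence is that this is a feasibility study and the sentence concerns a later one. The primary objective is the feasibility of the strategy, recruitment and data collection, and the progression thresholds rest on fidelity to CLECC-Pal and use of the 4AT. The article does not say that the ICC will be the only input or that a zero estimate would be used as it stands. Confidence limits and sensitivity ranges could well appear in a fuller document or in the later study's own plan. The stepped wedge is described as something to work towards. Restricting the ICC to pre-intervention data is also defensible, because follow-up records mix in differences between hospices in uptake.

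Much of this stands, and it limits the severity. It does not rescue the sentence, which goes beyond leaving a detail out: it names the data source and says what that source makes possible, and three hospices cannot deliver it.

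Three stronger readings are tempting, and the documents do not support them.

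- A reader might apply the usual design effect, 1 + 49 × 0.05 = 3.45, and conclude that the national study could be under-sized 3.45-fold. That formula is for parallel clusters. A stepped wedge draws partly on within-hospice comparisons, and Step 4 gives smaller ratios for the layouts tried.
- A reader might infer that the hospices were picked to differ, which would inflate the ICC. The article describes them as diverse but does not say that they were selected for it.
- A reader might infer that the study fails as a feasibility study. Nothing in the data-collection questions or the progression rule uses the ICC.

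**Conclusion.** The concern holds, at moderate severity. Pre-intervention data from three hospices cannot fix the ICC closely enough to determine the number of sites. The interval at an observed 0.05 runs from about 0 to 0.74, and the chance of an estimate at or below zero is between 14% and 48% over the assumed true range of 0.10 down to 0.01. The same data say nothing about between-period correlation. The claim that they enable a powered calculation is therefore wrong as written, and the fifth aim depends on it.

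The figures assume a normal outcome, equal blocks of 50 and true ICCs of 0.01 to 0.10. The 1.3- to 2.2-fold effect on variance also rests on an assumed layout and would change with another. The imprecision itself depends on the number of hospices, which the article fixes at three.

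**What to change.** Replace the Discussion sentence with wording such as: *The ICC from the pre-intervention data will be reported with its 95% confidence interval, for description only. The number of hospices and in-patient episodes for the national study will be calculated over a pre-stated range of ICC and between-period correlation, using external values where these are available. The feasibility data will supply the standard deviation and the event proportion.* The authors should choose the range and state it in advance; 0.01 to 0.10 is one example.

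Pooling the baseline and follow-up records would not solve the problem. It adds no hospices, so the between-hospice variance keeps 2 degrees of freedom, and records from week 4 of CLECC-Pal use would bring in differences in uptake.

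The cost is a change of wording and a sensitivity table, with no new data. The fifth aim would then deliver a range of site and episode numbers instead of a single figure. Whether suitable external ICCs exist cannot be judged from the article; if none do, the pre-stated range has to stand alone.
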